## Abstract

**Rationale:**

The increasing use of thrombectomy for acute ischemic stroke highlights the need to better understand its complications. Vessel perforation leading to active intracranial bleeding is a severe complication associated with a poor outcome and a mortality rate of approximately 50%. The etiology and risk factors for this severe complication remain largely unknown, and there is limited evidence to guide decision-making regarding endovascular hemostatic strategies and the continuation of thrombectomy after perforation.

**Design:**

The Perforation EVents during ENdovascular Therapy for acute ischemic stroke (PREVENT) Registry is an international, multicenter, prospective, and retrospective study, collecting data on vessel perforations during thrombectomy. The registry aims to include 500 cases of vessel perforation and 500 matched controls without perforation. The collected data will consist of both tabulated data and periprocedural imaging, which is to be analyzed centrally by an imaging core laboratory. Data will be analyzed using a case–control method, employing both univariate and multivariate statistical analyses.

**Objectives:**

The primary objectives of this study are to (1) identify risk factors for vessel perforation, (2) explore the underlying pathophysiology, (3) develop a classification system for vessel perforations, (4) compare different hemostatic treatment strategies, (5) evaluate the impact of continuing versus aborting thrombectomy after perforation, and (6) propose a safety-optimized thrombectomy technique.

**Discussion:**

Given the frequency and hyperacute nature of vessel perforations, a prospective randomized study is not feasible. This large, international registry provides a robust approach to collecting real-world evidence, reducing bias through multicenter data collection and case matching. The findings may help improve clinical decision-making and enhance patient safety during thrombectomy procedures.

**Clinical trial registration:**

ClinicalTrials.gov, identifier NCT06394180.

## Introduction

Stroke is the second leading cause of death and the leading cause of disability, both globally and in Europe (1, 2). Thrombectomy has revolutionized the treatment of acute ischemic stroke, following evidence from five randomized controlled trials demonstrating a substantial benefit in patients with large-vessel occlusion of the anterior circulation (3). Since then, the indications for thrombectomy have continued to expand (4), including patients with posterior circulation occlusions (5, 6), selected patients presenting late after symptom onset (7–9), and patients with large infarcts (10, 11). Patients with medium or distal vessel occlusions (MDVOs) are also increasingly being considered for thrombectomy (4, 12, 13). Two recent randomized controlled trials did not demonstrate the superiority of MDVO thrombectomy over best medical treatment alone (14, 15). One trial reported a higher number of symptomatic intracranial hemorrhages (sICHs) and a higher mortality in the thrombectomy group (14). A third trial was stopped early for futility and also reported a higher rate of sICH in the thrombectomy group compared to the best medical management group (16).

These findings might point towards a different aspect of thrombectomy: despite its effectiveness, the procedure is not without the risk of periprocedural complications. Intracranial vessel perforation with subsequent arterial bleeding occurs in 1–6% of thrombectomies (17–20). This complication is typically a critical event, with permanent consequences (21, 22) and a mortality rate of approximately 50% (17, 19, 23). Given the rapidly increasing number of thrombectomies, an increase in the incidence of periprocedural perforations is to be expected. This is particularly relevant for MDVO thrombectomy, as the incidence of vessel perforations has been reported to be twice that of LVO thrombectomy (17).

The available data on vessel perforations during thrombectomy are limited (21). It is unknown why some patients experience this complication, while the majority are spared. Similarly, the underlying pathophysiological process that leads to vessel wall damage is not understood. There is uncertainty about which patients benefit from endovascular hemostatic treatment to achieve cessation of active bleeding and whether temporary vessel occlusion (e.g., using an intracranial balloon catheter or by deploying coils without detachment) or permanent vessel occlusion (e.g., using liquid embolic agents or permanent coiling) is more appropriate. In addition, limited data are available on whether thrombectomy should continue after a perforation occurs or whether the procedure should be aborted. Given the low frequency of this complication and its hyperacute nature, randomized prospective trials are unlikely to be feasible.

## Methods and analysis

### Design

The Perforation EVents during ENdovascular Therapy for acute ischemic stroke (PREVENT) Registry is an international, multicenter, prospective, and retrospective observational study collecting data on vessel perforations during thrombectomy.

Data collection includes the following:

Patient baseline data (e.g., age, sex, pre-stroke modified Rankin Scale (mRS), pre-stroke anticoagulation or platelet therapy, and others).Data on the initial ischemic event (e.g., NIHSS at admission, number and location of vessel occlusions, TOAST classification [trial of ORG 10172 in Acute Stroke Treatment], imaging features related to clot composition, intracranial atherosclerotic disease (ICAD) or primary intracranial dissection, non-interventional stroke management, and other relevant factors).Details on circumstances and technique of the thrombectomy (e.g., anesthesiological management, type of aortic arch, cervical stenosis, thrombectomy technique, design and dimensions of the thrombectomy devices, operator experience, and others).Hemostatic therapy (e.g., non-endovascular hemostatic measures such as lowering of the systemic blood pressure or medication with coagulation effects, endovascular hemostatic measures including timing, exact mechanism, effectiveness, and other relevant factors).Outcome measures (e.g., functional outcomes including mRS at 90 days, and imaging outcomes including recanalization status, volume of intracranial hemorrhage, and other relevant factors).

The collected data are stored safely in a REDCap database. Periprocedural imaging and the first postinterventional CT or MRI are obtained for the extraction of quantifiable imaging parameters, exploration of patterns, and quantification of the volume of extravasated blood and contrast agents. Imaging data are stored in a safe, password-protected Picture Archiving and Communication System (PACS) at Basel University Hospital, Basel, Switzerland. The duration of active intracranial bleeding is derived from the time stamps of the digital subtraction angiography series during thrombectomy displaying contrast extravasation. The collateral status will be derived from the first intraprocedural angiographic run. The flow rate of extravasation (i.e., the volume of extravasation per second) will be classified by the imaging core laboratory based on the first angiographic run that demonstrates extravasation. This will be used as a surrogate for perforation magnitude. A semi-quantitative assessment of the flow rate of extravasation will be sought, if technically feasible. Imaging evaluation will be carried out by a central imaging core laboratory to ensure a consistent interpretation.

PREVENT exclusively consists of data and imaging that have initially been collected for clinical purposes of patient care. As an observational study, PREVENT does not contain a randomization.

PREVENT aims to answer the following questions:

Which risk factors are associated with the occurrence of vessel perforations during thrombectomy?Is it possible to identify distinct mechanisms of vessel perforation? Is it possible to describe pathophysiological phenomena associated with vessel perforation?Are there groups of perforations that can be distinguished in terms of risk profiles and the need for urgent complication management, on the basis of which a classification system can be created? If so, can a pathophysiological explanation be found for the differences between these groups?In patients with ongoing contrast extravasation, which individuals should receive endovascular therapy to achieve hemostasis? How do specific hemostatic strategies compare to others regarding efficacy and safety?In patients in whom ongoing contrast extravasation has stopped, should thrombectomy be continued, or should the procedure be aborted?Based on the insights gained from PREVENT, is it possible to design a safety-optimized thrombectomy technique that may be used if patient-related risk factors imply an increased risk of vessel perforation?

Figure 1 shows the aims of the PREVENT registry.

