### Selection/treatment of subjects

Adult patients (≥18 years) who underwent thrombectomy for acute ischemic stroke on or after 1 January 2015 and experienced a periprocedural vessel perforation will be included. Vessel perforation is defined as contrast extravasation in at least one angiography series. Patients will be excluded if intracranial hemorrhage was present on pre-interventional imaging, if vessel wall damage was due to intracranial dissection without active contrast extravasation, if vessel perforation was due to the rupture of a pre-existing intracranial aneurysm (i.e., extravasation originates from an aneurysmal outpouching or dilation of an intracranial artery on the first run that demonstrates extravasation), or if vessel perforation led to the development of an arteriovenous fistula (e.g., carotid-cavernous fistula), but not to subarachnoid hemorrhage.

To evaluate risk factors that predispose patients to perforations, PREVENT is designed as a case–control registry. For the inclusion of each patient who experiences a perforation during thrombectomy, one matched patient of the same sex and similar age, with acute ischemic stroke due to vessel occlusion in the same vascular segment and treated at the same center, but without perforation, will be included.

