### Data analysis

Summary tables for patient demographics as well as baseline and intervention characteristics will be provided. Further statistical analysis will be tailored for each of the study’s aims. The methods per aim are presented below, following the same order:

To identify risk factors associated with vessel perforations, we will, in the first stage, make comparisons between cases with and without perforation during thrombectomy for predefined risk factors. Statistical analyses will include paired samples *t*-test, Wilcoxon test, and chi-squared test or Fisher’s exact test. Furthermore, multivariable logistic regression models can be used to identify the association between multiple variables and the occurrence of vessel perforations.An exploratory analysis of the interventional image material in the central image analysis laboratory is planned. After reviewing the image material of approximately 20% of patients with explorative intention, imaging criteria will be defined with regard to possible mechanisms of vessel wall injury and distinct pathophysiological phenomena. These criteria will be used to classify the remaining 80% of patients. Due to the exploratory nature, no definitive statistical evaluation strategy can yet be determined.For this purpose, data-driven K-nearest neighbor clustering will be applied to identify different groups of similar patient characteristics. We will consider 2–4 clusters, and the distribution of the clusters will be inspected visually. After the identification of the clusters, we will compare the pathophysiological characteristics between the clusters.Patients with perforation will be divided into two groups: patients who received interventional hemostatic therapy after the perforation occurred—e.g., temporary intracranial balloon occlusion or permanent vessel occlusion with liquid embolization or coils—and patients who did not receive hemostatic therapy. Propensity score matching or inverse probability of treatment weighting will be used to control for the location of perforation and the flow rate of extravasation. The two groups will be compared with each other to identify differences in the duration of extravasation and in clinical outcomes. The appropriate statistical model will be used for each of the clinical outcomes (e.g., logistic regression model for binary outcomes and ordinal regression model for ordinal outcomes).Patients with perforation will be divided into two groups: patients in whom thrombectomy was continued after the perforation occurred and patients in whom the procedure was aborted. Propensity score matching or inverse probability of treatment weighting will be used to control for the amount of extravasation, stroke severity, occlusion location, collateral status, and other clinical outcome predictors. The two groups will be compared with each other to identify differences in clinical outcomes.The new insights on risk factors, mechanisms, and pathophysiology of vessel perforation will be gathered. An expert panel will discuss potential modifications to current thrombectomy workflows to reduce the risk of periprocedural perforation, both in response to specific patient-related risk factors (e.g., occlusion location and vessel tortuosity) and in general. No definitive statistical evaluation strategy can yet be determined.

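### Bleeding duration dated from series that show extravasation depends on clinical run timing, which puts the aim 4 comparison of duration at risk of bias of unknown direction

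*Protocol article*

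**What the plan says.** The protocol article, Design, fixes the source of the measurement: "The duration of active intracranial bleeding is derived from the time stamps of the digital subtraction angiography series during thrombectomy displaying contrast extravasation".

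The same section says how the images arose: "PREVENT exclusively consists of data and imaging that have initially been collected for clinical purposes of patient care". No acquisition schedule is imposed, so the operator decided when each run was taken.

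Under Selection/treatment of subjects, "Vessel perforation is defined as contrast extravasation in at least one angiography series", so a patient with exactly one positive series is eligible.

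Under Data analysis, the fourth aim divides perforation cases by receipt of interventional hemostatic therapy. It continues: "The two groups will be compared with each other to identify differences in the duration of extravasation and in clinical outcomes". Propensity score matching or inverse probability weighting "will be used to control for the location of perforation and the flow rate of extravasation".

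The registry also collects "endovascular hemostatic measures including timing, exact mechanism, effectiveness", but the article does not link these items to the definition of duration.

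**The concern.** For one continuous bleed, onset lies at or before the first positive run, and cessation lies between the last positive run and the first negative run after it. A duration built from positive runs alone has three weaknesses:

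- It cannot exceed the true duration, and the shortfall grows with the gap between runs.
- A bleed seen on one series has duration zero.
- A bleed still visible on the final run is treated as having ended there.

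These errors matter because duration is a named outcome of aim 4 and bears directly on whether hemostatic therapy works. If both groups are imaged at the same pace and followed until a run is negative, the shortfall is similar in each and largely cancels. If imaging pace or completeness depends on treatment, it does not cancel. A difference could then appear where there is none, or a real one could be hidden.

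Adjustment for location and flow rate does not address this, because run timing after the perforation is part of how the outcome is measured. Central reading standardises how a run is interpreted, not when it was taken. Reaching the planned 500 cases would narrow the interval around a biased estimate without moving it.

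**Working it through.** **Inputs.** The article gives no bleeding duration, run interval or figure for this comparison, so there is nothing to reproduce. All durations and gaps below are assumptions: true mean M of 10 min (other values where stated), and evenly spaced runs with gap d.

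**Formula.** Let the true duration be exponential and q = exp(-d/M). Counting from the first positive run, the mean of last positive minus first positive is d·q/(1-q). The share with a single positive run, and so duration zero, is 1-q.

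**Step 1: dependence on run spacing (M = 10).**

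| d (min) | q | mean measured (min) | share zero |
|---|---|---|---|
| 1 | 0.905 | 9.51 | 10% |
| 2 | 0.819 | 9.03 | 18% |
| 3 | 0.741 | 8.57 | 26% |
| 5 | 0.607 | 7.71 | 39% |
| 8 | 0.449 | 6.53 | 55% |

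A simulation with a random offset between onset and first run, and inclusion only if at least one run is positive, gives matching means: 9.5, 9.0, 8.6, 7.7 and 6.5 min. With a gamma distribution (shape 4, mean 10 min) the loss is larger: 9.0, 8.0, 7.1, 5.4 and 3.4 min.

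**Step 2: no true effect, spacing differs by group (treated minus untreated, M = 10).**

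- 2 v 5 min: 9.03 - 7.71 = about +1.3 min (simulated +1.37).
- 5 v 2 min: about -1.3 min (simulated -1.33). The exact values are equal and opposite; the gap between 1.37 and 1.33 is simulation error.
- 2 v 3 min: 9.03 - 8.57 = about +0.5 min (simulated +0.44).
- 3 v 8 min: 8.57 - 6.53 = about +2.0 min.
- Equal spacing, complete follow-up: 0.
- Gamma model, 2 v 5 min: 8.02 - 5.38 = about +2.6 min.

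**Step 3: a true effect with equal spacing.** With true means of 8 v 12 min (difference -4.0), the measured difference at equal gaps of 1, 3 and 5 min is -4.0, -4.0 and -3.9 min (exponential). Under the gamma model it is -4.0, -3.9 and -3.7 min. Equal spacing nearly preserves the contrast.

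**Step 4: equal spacing, unequal follow-up.** Both groups have d = 3 and M = 10, so q = 0.741. One group is imaged until a run is negative: 8.57 min. The other has its last run 9 min after the first positive one: 3(q + q² + q³) = 3(0.741 + 0.549 + 0.407) = 5.1 min, and q³ = 41% are still positive on that last run. If the last run is at 18 min, the mean is 8.57 × (1 - exp(-1.8)) = 7.2 min. Whichever group is followed for less time looks shorter.

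**Step 5: would a midpoint rule be enough?** Ending halfway to the first negative run adds d/2. For 2 v 5 min this gives 10.03 v 10.21, a difference of about 0.2 min. The near-cancellation is special to the exponential model: under the gamma model the midpoint means are 9.0 and 7.9 min.

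**The case against.** The strongest reply is that the article does not set out the rules criticised here. It does not say that positive series are the only source, that duration is last minus first, that one positive series scores zero, or that a positive final run counts as cessation. A condensed article may leave these to the full protocol or an imaging manual, and the sentence does not exclude the next negative run as an end point. This stands in part. These are consequences of the sentence taken as written, not rules the article spells out. But the sentence does state which series supply the time stamps, and that choice omits the run that bounds cessation.

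A reader might also infer that the aim 4 comparison is biased, and that treatment will look as if it prolongs bleeding because treated patients have more control runs. The documents do not support this. They give no run frequency by group, equal spacing with complete follow-up produces no spurious difference, and reversing the gaps reverses the sign. Closer imaging after treatment is plausible but not shown.

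Two further points are fair. The angiograms are collected, so no information is lost and the end rule can still be set. And the clinical outcomes compared in aim 4 are not measured from run time stamps, so this point does not touch them.

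**Conclusion.** The concern holds as a conditional risk. Taken as written, the definition understates duration by an amount set by unstandardised run timing, gives zero for a single positive series, and ends a still-visible bleed at the last run. The comparison of duration in aim 4 is at risk of bias if run spacing, or follow-up to a negative run, differs by treatment, and the named adjustment does not cover this. Neither the presence of such a difference nor its direction can be read from the article.

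With an assumed exponential mean of 10 min and no true effect, the spurious difference runs from 0 (equal spacing, complete follow-up) through about 1.3 min either way (2 v 5 min gaps) to about 2 min (3 v 8 min gaps). It is about 3.5 min (8.6 v 5.1) if one group's runs end 9 min after the first positive one. These sizes depend on the assumed durations and gaps and on one continuous bleed per patient. The definition should be changed before duration is analysed.

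**What to change.** - **Record** four time stamps per case: last negative run before extravasation, first positive, last positive and first negative after. Flag cases still positive on their last run.
- **Analyse** cessation as interval-censored between the last positive and first negative run, and as right-censored when the last run is positive, with the propensity weights already planned for aim 4.
- **Report** the number and spacing of runs, and the share followed to a negative run, by treatment group. This shows whether the risk is real in these data.
- **State as a limitation** that the model assumes run timing is independent of bleeding status given the covariates. Operators may image because they suspect bleeding or have just treated it, so the model reduces the problem but may not remove it.

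If the full protocol already dates cessation this way, only the article's sentence needs correcting.

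The cost is two extra time stamps per case, read from angiograms the core laboratory already holds, and wider intervals around the estimated difference. No new patient data are needed.

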**Figure 1 fig1:**
[figure not shown]
Aims of the PREVENT registry. PREVENT, Perforation EVents during ENdovascular Therapy for acute ischemic stroke.

### Selection/treatment of subjects

Adult patients (≥18 years) who underwent thrombectomy for acute ischemic stroke on or after 1 January 2015 and experienced a periprocedural vessel perforation will be included. Vessel perforation is defined as contrast extravasation in at least one angiography series. Patients will be excluded if intracranial hemorrhage was present on pre-interventional imaging, if vessel wall damage was due to intracranial dissection without active contrast extravasation, if vessel perforation was due to the rupture of a pre-existing intracranial aneurysm (i.e., extravasation originates from an aneurysmal outpouching or dilation of an intracranial artery on the first run that demonstrates extravasation), or if vessel perforation led to the development of an arteriovenous fistula (e.g., carotid-cavernous fistula), but not to subarachnoid hemorrhage.

To evaluate risk factors that predispose patients to perforations, PREVENT is designed as a case–control registry. For the inclusion of each patient who experiences a perforation during thrombectomy, one matched patient of the same sex and similar age, with acute ischemic stroke due to vessel occlusion in the same vascular segment and treated at the same center, but without perforation, will be included.

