By focusing exclusively on vessel perforations during thrombectomy, the PREVENT registry represents a dedicated effort to target a specific safety aspect of thrombectomy. Unlike prospective randomized trials, which would be unfeasible due to the rarity and acute nature of this complication, PREVENT allows for the collection of a large, real-world dataset across multiple institutions. The matched case–control approach enables comparisons between patients with and without perforation under otherwise similar conditions. This may help to identify characteristics of the patient (e.g., neurovascular risk factors), the procedure setting (e.g., anesthesiologic strategy), or the devices (e.g., dimensions in relation to vessel diameters) that might be associated with increased risks. Additionally, the centralized imaging analysis ensures a standardized interpretation of angiographic and postprocedural imaging, allowing for the identification of distinct pathophysiological patterns of vessel perforation. A comparison between different hemostatic strategies (e.g., medical management only, temporary vessel occlusion, and permanent vessel occlusion) may provide insights into their effectiveness. By leveraging data that have been previously collected in routine clinical practice, PREVENT circumvents ethical and logistical barriers inherent in interventional trials while still providing robust insights into the mechanisms, management, and potential prevention of vessel perforations in thrombectomy.

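### Matching on segment, sex, centre and age makes their main effects inestimable from the pairs, and leaving procedure date out of the matching rule lets calendar period confound device and technique comparisons

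*Protocol article*

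**What the plan says.** The protocol article gives the purpose of the control group under Selection/treatment of subjects: "To evaluate risk factors that predispose patients to perforations, PREVENT is designed as a case–control registry". Every case is to be paired with "one matched patient of the same sex and similar age". The rule goes on to require that this control be someone "with acute ischemic stroke due to vessel occlusion in the same vascular segment and treated at the same center, but without perforation". The planned size is given in the Abstract, Design: "The registry aims to include 500 cases of vessel perforation and 500 matched controls without perforation".

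Two other parts of the article bear on location. The Introduction motivates the work for medium and distal vessel occlusions (MDVO) by noting that "the incidence of vessel perforations has been reported to be twice that of LVO thrombectomy". Under Data analysis, aim 6 has an expert panel discuss workflow changes "in response to specific patient-related risk factors (e.g., occlusion location and vessel tortuosity) and in general". The matching question in Methods (Design) ties aim 6 to what the registry itself has taught.

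On time, eligible patients are those "who underwent thrombectomy for acute ischemic stroke on or after 1 January 2015", enrolled both retrospectively and prospectively. The Discussion observes that thrombectomy technique keeps changing. It also says that the matched approach "enables comparisons between patients with and without perforation under otherwise similar conditions" and names procedure setting and devices among the characteristics to be examined. For aim 1, Data analysis commits to paired t, Wilcoxon, chi-squared or Fisher tests. Multivariable logistic regression is offered as an option, with no covariates named.

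**The concern.** A factor on which controls are matched has no contrast left within pairs. Segment, sex and centre are fixed exactly and age approximately, so the matched set cannot show whether any of them raises the risk of perforation. Matching on segment is a reasonable choice for studying other factors. The difficulty is that aim 6 presents occlusion location as something to act on in light of the registry's insights. A reader who sees equal location distributions in cases and controls could take that as evidence of no location effect.

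The second part runs the other way: a factor that probably should be controlled is not in the rule. A case and its control at the same centre may be years apart. Devices, technique and anaesthesia are the exposures most likely to shift with calendar time, and the tests to which the article commits for aim 1 do not adjust for date. If controls tend to come from a different period than cases, an exposure with no effect can look protective or harmful.

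**Working it through.** The article gives no odds ratio, alpha or power for aim 1, so there is no stated figure to reproduce. Inputs marked *assumed* are illustrative.

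**1. Location**

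Inputs: 500 cases and 500 controls (article); MDVO to LVO (large-vessel occlusion) risk ratio of 2 (Introduction); LVO perforation risk 1–3% and MDVO share of thrombectomies 20–40% (*assumed*); two-sided 0.05 (*assumed*).

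Worked case with LVO risk 1%, MDVO risk 2% and MDVO share 30%:

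- MDVO share among cases: 0.3×0.02 / (0.3×0.02 + 0.7×0.01) = 0.006/0.013 = 0.462.
- MDVO share among controls not matched on segment: 0.3×0.98 / (0.3×0.98 + 0.7×0.99) = 0.294/0.987 = 0.298.
- Odds ratio without segment matching: (0.462/0.538) / (0.298/0.702) = 2.02.
- Segment-matched controls have the case distribution, 0.462. The crude odds ratio is 1.00. There are no segment-discordant pairs, so the conditional odds ratio is not estimable.

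Over the whole assumed range, unmatched controls would give odds ratios of 2.02–2.06 with power above 99% at 500 per group. Segment-matched controls give 1.00 whatever the truth. The same reasoning applies to sex and centre, and nearly so to age.

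**2. Procedure date**

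Inputs (all *assumed*): a technique with no effect on perforation, used in 20% of early-era and 60% of late-era procedures; 50% of cases from the early era.

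| Controls from early era | Use in cases | Use in controls | Crude odds ratio (truth 1.00) |
|---|---|---|---|
| 50% | 0.5×0.2 + 0.5×0.6 = 0.40 | 0.40 | 1.00 |
| 40% | 0.40 | 0.4×0.2 + 0.6×0.6 = 0.44 | (0.40/0.60)/(0.44/0.56) = 0.85 |
| 25% | 0.40 | 0.25×0.2 + 0.75×0.6 = 0.50 | (0.40/0.60)/(0.50/0.50) = 0.67 |

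The direction depends on which group is more recent. With 60% of controls from the early era, use in controls is 0.6×0.2 + 0.4×0.6 = 0.36 and the odds ratio is (0.40/0.60)/(0.36/0.64) = 1.19.

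A second set of assumptions shows the effect on testing. Use is 20% early and 70% late, with 50% of cases and 70% of controls from the late era. Use is then 0.45 in cases and 0.3×0.2 + 0.7×0.7 = 0.55 in controls, and the odds ratio is (0.45/0.55)/(0.55/0.45) = 0.67. An unadjusted two-sided 5% test at 500 per group rejects the true null in 89% of studies. In 500 simulated data sets for this setting, adding a period term to an ordinary (unconditional) logistic regression brought the average odds ratio back to 1.00, with 4.2% rejections.

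**The case against.** On location, the article nowhere plans a location odds ratio. Aim 1 refers to predefined risk factors without listing location, and the Discussion's examples for the matched comparison are patient, setting and device characteristics, with segment acting as a control variable. In aim 6, the sentence on gathering insights is separate from the one naming location, and the panel could draw on the twofold incidence already cited. Location as an effect modifier, mechanisms by site among the 500 cases, and tortuosity, which is not matched, all remain open to study. This stands. A reader might infer that the registry cannot inform location at all, or that aim 6 is invalid; the article supports neither. What remains is narrower: the main effect is lost, no later analysis of these 1,000 patients recovers it, and the article does not say so while linking aim 6 to its own insights.

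On date, the matching rule is one sentence in a condensed article. A date window or a covariate list may sit in a fuller protocol or analysis plan that is not shown, and the optional regression could include date. Nothing in the article says that case and control dates differ. This also stands in part. A reader might infer that device and technique results will be confounded; the article does not show that, because the bias requires unequal calendar distributions and the uptake figures are assumed. But the rule as stated lists its matching factors and date is not among them, and the analyses that are promised, as opposed to permitted, leave date unadjusted.

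**Conclusion.** The point holds in two limited statements.

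- Main effects of segment, sex and centre, and essentially of age, are not estimable from the matched pairs. This follows from the matching rule alone and needs no assumption. Any location-based main-effect risk used in aim 6 must come from outside the pairs.
- Device, technique and anaesthesia associations can be confounded by calendar period unless date is matched or adjusted for. The size is not known from the article. Under the 20% to 60% uptake assumed above, an imbalance of 10–25 percentage points in the early-era share moves a null odds ratio to 0.85–0.67; with equal calendar distributions it stays at 1.00.

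Both can be settled by a clearer statement of the design and one addition to control selection. Neither undermines the case–control approach for unmatched factors.

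**What to change.** 1. State that main effects of segment, sex, centre and age will be neither estimated nor interpreted from the pairs. Examine segment only as an effect modifier in the matched analysis, or descriptively within cases. In aim 6, say that any main-effect risk attributed to occlusion location comes from external evidence.
2. Among controls who meet the existing criteria, select the one whose procedure date is closest to that of the case. Include procedure date in the matched (conditional) regression, also for pairs already enrolled, and use that model rather than the unadjusted tests for device, technique and anaesthesia associations.

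The cost is slightly looser age matching and one more model term. Close date matching also means that a calendar trend in perforation risk cannot be read from the pairs, so date joins the list in item 1. If the sponsor wants its own location effect, centre totals of thrombectomies by segment and year would supply a denominator. That is new data collection across an international registry and should be optional.
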